### Measurements

Baseline characteristics, including gender, age, body height and weight, abdominal circumference, complications, duration of T2DM, background treatment, and smoking and drinking habits will be recorded prior to randomization. The status of the study medications and the participant’s background treatment will be recorded at each visit. Measurements of BP, pulse rate, BW, and body mass index (BMI) will also be carried out at baseline and after 12 and 24 months. Abdominal circumference will be measured at baseline and 24 months. Blood tests without HbA1c level will be checked at baseline and 24 months (details listed in Additional file 2); HbA1c will be measured at baseline and after 12 and 24 months. Specific biomarkers such as N-terminal pro-brain natriuretic peptide (NT-proBNP), high-sensitivity C reactive protein (hsCRP), high-molecular weight adiponectin, and malondialdehyde modified low-density lipoprotein (MDA-LDL) will be measured at baseline and 24 months. Creatinine-corrected urinary albumin excretion will be measured at baseline and 24 months (optional). Some optional imaging and physiological tests are also planned in the study including abdominal computed tomography to measure the amount of visceral and subcutaneous fat, echocardiograms, flow-mediated dilation (FMD), pulse-wave velocity (PWV), cardio-ankle vascular index (CAVI), and augmentation index (AI) (details listed in Additional file 3).

#### Measurement of carotid IMT

The protocol and method for measuring carotid IMT have been described in detail previously [25, 31, 32]. In brief, the carotid ultrasound examinations using standardized imaging protocols and systems equipped with >7.5 MHz linear transducers will be performed at each local site and then measured at a core laboratory (Tsukuba University) at baseline and 24 months after randomization. Expert trained sonographers who have attended a lecture on measuring carotid IMT will carry out the procedure according to the Mannheim carotid IMT consensus [33, 34]. The head position and probe angle of the ultrasound approach will be set using a ruler located just cephalad (Fig. 2). Longitudinal B-mode images, perpendicular to the ultrasound beam, with a 3–4 cm imaging depth, will be recorded in the distal common carotid arteries (CCA), carotid bulbs, and proximal internal carotid arteries (ICA) on both sides. The lateral probe incidence is used to obtain CCA images, using external landmarks and an original semicircular protractor developed for this purpose. The mean CCA-IMT indicates the average IMT value of the right and left CCA-IMT, 10 mm from the bulb. The following far wall IMTs will be measured; maximum IMT of the CCA and mean and maximum IMTs of the bulb and ICA. The optimized R-wave gated still frames of the carotid IMT will be stored as JPEG files, with all the parameters collected and measured at the core laboratory. An expert analyzer blinded to the allocation and clinical information of the subjects will measure all the IMT values using an automatic IMT measurement software program (Vascular Research Tools 5, Medical Imaging Applications, Iowa, USA) [35]. The software program identifies the lumen/intima and the media/adventitia borders in this region and calculates the distance between them.

**Fig. 2 Fig2:**
[figure not shown]
Method for measuring IMT. **a** Head position is set at 45° toward the other side (*right*) when measuring at the left carotid artery. **b** The probe angle is also set at 45° using the ruler on the test side. **c** A plus B. **d** Schema for measuring the left carotid artery. The probe is set perpendicular to the sagittal plane

### Safety

Based on the intention-to-treat the entire population, safety will be checked by recording the following adverse effects (AEs) throughout the study: severe AEs regardless as to whether or not there is causal relationship between the AEs and the study; and relevant AEs such as hypoglycemia, genital or urinary tract infections, ketoacidosis, and hypovolemic symptoms. When the investigators confirm these AEs, the grade of severity, procedures, outcomes, and relationship to the study drug will be assessed. A prompt report to the study secretariat and to the Data and Safety Monitoring Board (DSMB) will then be made by the trial organizer. The members of the DSMB consist of authorized endocrinologists, cardiologists, or neurologist with relevant expertise. The criteria for withdrawal from the trial are listed in Table 2. The incident of withdrawal from the study will be reported promptly to the DSMB by the chief investigator. The DSMB will then deliberate on the incident and report the decision to the chief investigator.

**Table 2 Tab2:** Discontinuance criteria

Severe hypoglycemia
Seriously poor glycemic control such as ≥HbA1c 12.0 % confirmed by second measurement on different day
Offer for participation declined by participants
Deviancy of eligibility after registration
Considered inappropriate to continue the study by investigators due to aggravation of primary disease or complications
Considered inappropriate to continue the study by investigators due to adverse side effects of the study drug
Pregnant
Poor drug adherence (<75 %, or >120 %)
Considered inappropriate to continue the study by investigators due to some other reason

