### Randomization and treatment

Eligible participants with appropriately signed informed consent will be randomized to either the ipragliflozin group or control group (ratio 1:1) using the web-based minimization method with biased coin assignment balancing [27, 28] for age (<65, ≥65 year), HbA1c level (<7.0, ≥7.0 %), systolic BP (<135, ≥135 mmHg), use of statins, and use of biguanides at the time of screening.

All participants will be followed-up for 24 months. Although a specific numerical goal in glycemic control such as HbA1c level is not set for the study, all participants need to be treated to achieve a personalized goal recommended by the treatment guideline in Japan (details in Additional file 1) [26]. Participants who are assigned to the ipragliflozin group receive ipragliflozin 50 mg once daily in addition to their background medical therapy. In accordance with official recommendation regarding use of SGLT2 inhibitor from the Japan Diabetes Society [29], patients aged ≥75 years should be most carefully followed up with particular attention to development of volume depletion-related adverse drug reactions [30]. If the personalized goal is not achieved, the dose of ipragliflozin can be increased by the investigators to 100 mg once daily. Participants who are assigned to the control group continue their background therapy. Within the appropriate range of the therapeutic goal, the participant’s background therapy will be, in principle and if possible, unchanged during the study in both groups. However, if participants cannot achieve their glycemic goal, co-administration of anti-diabetic agents other than SGLT2 inhibitors or increased dosages of the other anti-diabetic agents in both groups may be considered by investigators, with caution being taken to prevent the development of hypoglycemia. However, because pioglitazone is known to have a suppressive effect on the progression of IMT, compared to glimepiride [22], it is prohibited to prescribe it or change its dose during the study. After the study is completed, all participants can continue any anti-diabetic treatment in accordance with their individual condition.

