### Statistical considerations

#### Sample size estimation

Due to the lack of data on the effect of SGLT2 inhibitors on carotid IMT, we referred to the statistical data from the CHICAGO study [22] and PROLOGUE study [25]. In the CHICAGO study, pioglitazone caused a significant inhibition of the progression of CCA-IMT (−0.0010 mm after 72 weeks), compared to glimepiride (+0.0120 mm after 72 weeks). We estimated the changes from baseline would be −0.0013 mm (pioglitazone) and +0.016 mm (glimepiride) after 96 weeks. Based on the assumption that ipragliflozin may inhibit the progression of CCA-IMT to the same extent as pioglitazone, we estimated the group difference as 0.016 (ipragliflozin −0.001 and control +0.015) ±0.06 (standard deviation). At a significant level of 5 % (two-sided), the sample size of 222 patients per arm provides a power of 80 % for each comparison. Allowing for a dropout rate of 5 %, 240 patients in each arm (a total of 480 patients) provides sufficient statistical power for the study.

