#### Statistical analysis plan

The analyses of the primary and secondary endpoints will be performed in the full analysis set (FAS), which includes all participants who received at least one dose of treatment during the study period and did not have any serious violation of the study protocol such as not providing informed consent, registration outside of the study period, or data collected after commencement of treatment.

Summary statistics will be calculated for the baseline characteristics including the frequencies and proportions for categorical variables and means ± standard deviations for continuous variables. The patient characteristics will be compared using Chi square tests for categorical variables, t tests for normally distributed continuous variables, or the Wilcoxon rank sum tests for continuous variables with a skewed distribution.

The analysis plan is similar to that used in previous studies we have conducted [25, 31, 32]. In brief, for the primary analysis comparing treatment effects, the baseline-adjusted means and their 95 % confidence intervals, estimated by analysis of covariance of the change in average carotid IMT at 24 months, will be compared between the treatment groups (ipragliflozin group vs. control group). The results will be adjusted by allocation factors. The primary analysis will not include missing observations, with the mixed effects model for repeated measures (MMRM) being used as a sensitivity analysis to examine the effect of missing data. In addition, MMRM will be used as a sensitivity analysis to examine the outcomes at baseline and 24 months modelled as a function of time, treatment, and treatment-by-time interaction. The secondary analysis will be performed in the same manner as the primary analysis.

All comparisons are planned and all *P* values will be two sided. *P* values <0.05 will be considered statistically significant. All statistical analyses will be performed using SAS software version 9.4 (SAS Institute, Cary, NC, USA). The statistical analysis plan will be developed by the principal investigator and a biostatistician before completion of patient recruitment and database lock.

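### Table 2 makes poor adherence and study-drug side effects grounds for leaving the trial; unless those participants are still scanned at 24 months, the complete-case primary analysis can be biased

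*Protocol article*

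**What the plan says.** All places are in the Protocol article.

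- **Safety:** "The criteria for withdrawal from the trial are listed in Table 2". Table 2 itself is headed as discontinuance criteria. It includes "Poor drug adherence (<75 %, or >120" per cent), investigator judgement that side effects of the study drug make it inappropriate to continue the study, HbA1c of 12% or more on confirmation, severe hypoglycaemia, "Deviancy of eligibility after registration", and an open investigator-judgement item.
- **Randomization and treatment:** "All participants will be followed-up for 24 months". The control group continues its background therapy and is given no study drug.
- **Measurement of carotid IMT:** scans are read at two time points only, baseline and 24 months. No separate arrangement is described for participants who have met a Table 2 criterion.
- **Statistical analysis plan:** the primary ANCOVA is run in a full analysis set (FAS) that requires at least one dose and no serious protocol violation. "The primary analysis will not include missing observations". MMRM is the stated sensitivity analysis for missing data, modelling baseline and 24 months.

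**The concern.** The trial asks what adding ipragliflozin to standard care does to IMT over 24 months. That question needs the 24-month outcome of participants who stop the drug or take it badly, as well as of those who persist with it.

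The text allows a different result. A participant who takes too little drug, or does not tolerate it, leaves the trial. With no scan, that participant has no primary endpoint and drops out of the ANCOVA. A control patient with the same habits and the same prognosis has no study drug to fail on and stays in. Randomisation then no longer protects the comparison on the characteristics that go with adherence and tolerability.

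The planned difference is small (0.016 mm against an SD of 0.06 mm, about 0.27 SD), so modest selection matters. A scan that was never taken cannot be recovered by any later analysis.

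**Working it through.** **1. The plan's own figure.** Inputs from Sample size estimation: "we estimated the group difference as 0.016" mm; SD 0.06 mm; "At a significant level of 5 % (two-sided"); "the sample size of 222 patients per arm provides a power of 80" per cent; 5% dropout; 240 per arm.

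- n per arm = 2 × (1.96 + 0.842)² × 0.06² / 0.016² = 220.7, so 221. The t-test solution is 221.7, so 222. The stated figure reproduces.
- 222 / 0.95 = 233.7, so 234; the plan rounds up to 240.
- 240 × 0.95 = 228 per arm analysed at the planned dropout, with power 81%.

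The sample size is not in dispute. It supplies the scale for what follows.

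**2. Which criteria act in which arm.**

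| Table 2 criterion | Ipragliflozin | Control |
|---|---|---|
| Side effects of the study drug | yes | no study drug |
| Poor drug adherence | yes | in practice no, if it means study drug |
| HbA1c of 12% or more, severe hypoglycaemia, pregnancy, refusal, late ineligibility, other judgement | yes | yes |

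The asymmetry concerns tolerability and adherence, not the whole table.

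**3. Illustrative bias with no true effect.** Let d be the share of the ipragliflozin arm selectively withdrawn and unscanned, and g the excess IMT progression of those patients over the retained ones. The whole-arm mean is the retained mean plus d × g, so the complete-case difference is shifted by d × g in favour of ipragliflozin when g is positive. Neither d nor g is in the document; both are assumptions. With 240(1 − d) against 228 analysed, SE = 0.06 × √(1/[240(1 − d)] + 1/228). Two-sided type I error = Φ(bias/SE − 1.96) + Φ(−bias/SE − 1.96).

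| d | g (mm) | bias (mm) | share of 0.016 | SE (mm) | type I error |
|---|---|---|---|---|---|
| 5% | 0.02 | 0.0010 | 6% | 0.00562 | 5.4% |
| 5% | 0.03 | 0.0015 | 9% | 0.00562 | 5.8% |
| 10% | 0.02 | 0.0020 | 13% | 0.00570 | 6.4% |
| 10% | 0.03 | 0.0030 | 19% | 0.00570 | 8.2% |
| 15% | 0.02 | 0.0030 | 19% | 0.00578 | 8.1% |
| 15% | 0.03 | 0.0045 | 28% | 0.00578 | 12.2% |

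**4. Does the MMRM help?** With one post-baseline value, a participant who lacks it contributes only a baseline. A simulation of 2,000 null trials (240 per arm) removed the 10% of the ipragliflozin arm highest on an unmeasured prognostic factor. Mean estimates were 0.0001 mm with full data, −0.0054 mm with complete-case ANCOVA and −0.0054 mm with the two-time-point likelihood model. The selection here was stronger than in the table, since (0.0054 + 0.0001) / 0.10 = 0.055 mm. The run therefore compares the two methods and is not an estimate of the likely bias.

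**5. Cost of measuring everyone.** If a share d stops and gets no benefit (assumption), the expected difference is 0.016 × (1 − d). At 228 per arm, SE = 0.06 × √(2/228) = 0.00562 and power = Φ(difference/SE − 1.96).

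| d | difference (mm) | power |
|---|---|---|
| 0 | 0.0160 | 81% |
| 5% | 0.0152 | 77% |
| 10% | 0.0144 | 73% |
| 15% | 0.0136 | 68% |

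**The case against.** The missing scan is inferred. Nowhere does the article say that a withdrawn participant is not scanned. It promises 24-month follow-up for all, and the full protocol may settle the matter. This stands, and it is why the point is conditional. What remains is a conflict between two statements that are both in print.

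A reader might infer that the primary result is simply a one-sided per-protocol comparison. The document does not support that. The FAS does not exclude non-adherers, so a withdrawn participant who was nevertheless scanned could be analysed, and most Table 2 criteria can apply in either arm. The adherence row also speaks of drug adherence without naming the study drug, and background treatment is recorded at each visit. That this row acts in one arm is a likely reading that rests on controls having no study drug.

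A reader might also infer that the bias must favour ipragliflozin. That is unproven. Nothing in the document says that patients who stop for side effects progress faster, and losing poorly controlled controls would make the control arm look better, which works against ipragliflozin.

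Finally, the only documented loss is 5% overall, and at 5% the illustrated bias is small. The assumed 0.02-0.03 mm excess has no source in the document and is larger than the whole assumed control progression of 0.015 mm. Both objections stand as limits on the size.

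The planned MMRM is a fair thing to cite in the plan's defence, but with two time points it does not test this bias.

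**Conclusion.** The concern holds in conditional form. The article defines withdrawal from the trial by criteria that include study-drug side effects and drug adherence, promises 24-month follow-up for everyone, and bases the primary analysis on observed 24-month values. If withdrawn participants go unscanned, the ipragliflozin arm is filtered on tolerability and, in practice, adherence, while the control arm is not. The FAS label and the MMRM do not prevent this.

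Size and direction cannot be known from the document. Under the stated assumptions the effect on type I error ranges from negligible at the planned 5% loss to roughly a doubling (about 12%) at 15% selectively withdrawn with 0.03 mm excess progression. It does not follow that the result will be biased, or biased towards benefit. The text leaves the primary comparison open to a bias that is avoidable now and not repairable once the 24-month visits have been missed.

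**What to change.** - Leave the reasons for stopping study drug as they are. State that meeting a Table 2 criterion does not end follow-up, and reconcile Table 2 and its lead-in sentence with the commitment to follow all participants for 24 months.
- Obtain the 24-month carotid scan in every randomised participant who has not withdrawn consent to follow-up, and include it in the primary analysis under the allocated arm.
- Use adherence of 75-120% only to define a per-protocol sensitivity set.
- For scans that are still missing, add a sensitivity analysis that allows for data missing not at random, because the two-time-point MMRM cannot serve that purpose.

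The cost is protocol wording plus scans already planned for 480 participants. The real downside is dilution of the effect, with the power loss shown in the working. That loss reflects the effect of adding ipragliflozin to care, which is the question the trial sets out to answer.

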### Study endpoints

Intima-media thickness (IMT) in the carotid artery is well-established as a surrogate marker for risk of CV diseases and is also useful for evaluating the effectiveness of various types of therapeutic interventions in patients with or without T2DM [35–37]. The primary endpoint in the study is the change in mean IMT of the CCA from baseline to 24 months. The secondary endpoints are the values and changes in parameters after 24 months of treatment, including: (1) mean IMT of the bulb and ICA, (2) max IMT of the CCA, bulb, and ICA, (3) the overall mean of mean IMT of the CCA, bulb, and ICA, (4) the mean of max IMT of the CCA, bulb, and ICA, (5) specific biomarkers including hsCRP, MDA-LDL, NT-proBNP, and high-molecular weight adiponectin, (6) the cardiovascular functional tests listed in Additional file 3 (optional), (7) abdominal circumference and amount of visceral and subcutaneous fat measured by abdominal computed tomography (optional), (8) creatinine-corrected urinary albumin excretion. In addition, the values and changes after 12 and 24 months in several clinical parameters including BP, BW, and BMI and laboratory data (details listed in Additional file 2) will be evaluated. Safety endpoints also include AEs and adverse drug reactions observed during the study.

### Statistical considerations

#### Sample size estimation

Due to the lack of data on the effect of SGLT2 inhibitors on carotid IMT, we referred to the statistical data from the CHICAGO study [22] and PROLOGUE study [25]. In the CHICAGO study, pioglitazone caused a significant inhibition of the progression of CCA-IMT (−0.0010 mm after 72 weeks), compared to glimepiride (+0.0120 mm after 72 weeks). We estimated the changes from baseline would be −0.0013 mm (pioglitazone) and +0.016 mm (glimepiride) after 96 weeks. Based on the assumption that ipragliflozin may inhibit the progression of CCA-IMT to the same extent as pioglitazone, we estimated the group difference as 0.016 (ipragliflozin −0.001 and control +0.015) ±0.06 (standard deviation). At a significant level of 5 % (two-sided), the sample size of 222 patients per arm provides a power of 80 % for each comparison. Allowing for a dropout rate of 5 %, 240 patients in each arm (a total of 480 patients) provides sufficient statistical power for the study.

#### Statistical analysis plan

The analyses of the primary and secondary endpoints will be performed in the full analysis set (FAS), which includes all participants who received at least one dose of treatment during the study period and did not have any serious violation of the study protocol such as not providing informed consent, registration outside of the study period, or data collected after commencement of treatment.

Summary statistics will be calculated for the baseline characteristics including the frequencies and proportions for categorical variables and means ± standard deviations for continuous variables. The patient characteristics will be compared using Chi square tests for categorical variables, t tests for normally distributed continuous variables, or the Wilcoxon rank sum tests for continuous variables with a skewed distribution.

The analysis plan is similar to that used in previous studies we have conducted [25, 31, 32]. In brief, for the primary analysis comparing treatment effects, the baseline-adjusted means and their 95 % confidence intervals, estimated by analysis of covariance of the change in average carotid IMT at 24 months, will be compared between the treatment groups (ipragliflozin group vs. control group). The results will be adjusted by allocation factors. The primary analysis will not include missing observations, with the mixed effects model for repeated measures (MMRM) being used as a sensitivity analysis to examine the effect of missing data. In addition, MMRM will be used as a sensitivity analysis to examine the outcomes at baseline and 24 months modelled as a function of time, treatment, and treatment-by-time interaction. The secondary analysis will be performed in the same manner as the primary analysis.

All comparisons are planned and all *P* values will be two sided. *P* values <0.05 will be considered statistically significant. All statistical analyses will be performed using SAS software version 9.4 (SAS Institute, Cary, NC, USA). The statistical analysis plan will be developed by the principal investigator and a biostatistician before completion of patient recruitment and database lock.

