**Methods:**

A total of 480 participants with type 2 diabetes mellitus with a HbA1c between 6 and 10 % despite receiving diet/exercise therapy and/or standard anti-diabetic agents for at least 3 months, will be randomized systematically (1:1) into either ipragliflozin or control (continuation of conventional therapy) groups. After randomization, ipragliflozin (50–100 mg once daily) will be added on to the background therapy in participants assigned to the ipragliflozin group. The primary endpoint of the study is the change in mean intima-media thickness of the common carotid artery from baseline to 24 months. Images of carotid intima-media thickness will be analyzed at a central core laboratory in a blinded manner. The key secondary endpoints include the change from baseline in other parameters of carotid intima-media thickness, various metabolic parameters, and renal function. Other cardiovascular functional tests are also planned for several sub-studies.

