## Methods

### Study overview and design

The PROTECT study is an ongoing, multicenter, prospective, randomized, open-label, blinded-endpoint, parallel group, investigator-initiated clinical trial (phase IV). The study will test the hypothesis that compared to standard care alone, the addition of ipragliflozin to standard care in T2DM may suppress the progression of carotid atherosclerosis, accompanied by an improvement in glycemic and lipid metabolism and vascular function. After recruitment and randomization of the patients into groups with or without ipragliflozin, each treatment is continued for 24 months, and the long-term safety and effects of ipragliflozin on CV systems then evaluated.

The study protocol was approved by the local institutional review boards and independent ethics committees. The study will be conducted in full compliance with the articles of the Declaration of Helsinki and according to the Ethical Guidelines for Medical and Health Research Involving Human Subjects established by the Ministry of Health, Labour, and Welfare and Ministry of Education, Culture, Sports, Science, and Technology. The PROTECT study was registered by the UMIN in July 2015 (ID: 000018440).

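### The efficacy set requires at least one dose of treatment, a condition with no common meaning when the control arm has no study drug, and one of its violation examples is misworded

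*Protocol article*

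**What the plan says.** The Statistical analysis plan section of the protocol article assigns the primary and secondary endpoints to a full analysis set that "includes all participants who received at least one dose of treatment during the study period and did not have any serious violation" of the protocol. Violations are given by example: "such as not providing informed consent, registration outside of the study period, or data collected after commencement of treatment".

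Three other places decide how that rule works:

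- Study overview and design calls the study a "prospective, randomized, open-label, blinded-endpoint, parallel group, investigator-initiated clinical trial".
- Randomization and treatment adds ipragliflozin to background therapy in one arm. For the other it says: "Participants who are assigned to the control group continue their background therapy".
- The Abstract (Methods) admits patients above the HbA1c threshold "despite receiving diet/exercise therapy and/or standard anti-diabetic agents for at least 3 months", so background therapy can be diet and exercise without any drug. Table 1 agrees.

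**The concern.** A one-dose condition is usually harmless in a double-blind placebo trial. Both arms have something to start, and failing to start cannot depend on known allocation. Neither holds here. Patients and physicians know the arm, and only one arm has a new treatment to decline. A patient allocated to ipragliflozin who never takes it can leave the primary analysis, while a comparable patient allocated to control stays in. The comparison is then no longer strictly between the groups as randomised, in a trial planned to detect only 0.016 mm.

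The last violation example adds a separate difficulty. It contains no word limiting it to baseline data, although the primary endpoint is a change to 24 months and depends on data gathered during treatment.

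**Working it through.** **1. What the dose condition does under each reading**

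| Meaning of treatment | Ipragliflozin arm | Control arm |
|---|---|---|
| Ipragliflozin | never-starters removed | everyone removed |
| Assigned therapy, including background drugs | never-starters can be removed | medicated patients pass automatically; diet-and-exercise patients have no dose |
| Condition waived for controls | never-starters removed | nobody removed |

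The first reading cannot be intended. The other two still act differently by arm.

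**2. The third example**

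Study endpoints defines the primary endpoint as change from baseline to 24 months, and Measurement of carotid IMT schedules the 24-month scan. A scan the protocol requires cannot be a violation of it, so the example must concern baseline data obtained too late. Even so repaired, it lacks a common reference date: ipragliflozin patients commence a treatment after randomisation, whereas controls continue what they already had.

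**3. The plan's own sample size**

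Inputs from Sample size estimation: difference 0.016 mm, SD 0.06 mm, two-sided 5%, power 80%.

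- Normal approximation: n = 2 × (1.960 + 0.842)² × 0.06² / 0.016² = 221 per arm.
- Two-sample t-test: 222 per arm (power 0.8005), as stated.
- Dropout: 222 / 0.95 = 234, which the plan takes up to 240. After 5% loss, 240 × 0.95 = 228 remain.

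There is no numerical error here.

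**4. Illustrative size of the shift**

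The article gives no never-starter rate, so these inputs are assumptions. Let k be the share of the ipragliflozin arm excluded among those with a 24-month scan, and g the difference in mean change between excluded and retained patients. Then shift = k × g.

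- k = 5% (12 of 240), g = 0.016 mm (never-starters progress like controls): 0.05 × 0.016 = 0.0008 mm, or 5% of 0.016.
- k = 5%, g = 0.03 mm: 0.05 × 0.03 = 0.0015 mm, or 9% of 0.016.
- Standard error of the difference: 0.06 × √(2/222) = 0.0057 mm. The shifts are 0.0008 / 0.0057 = 0.14 and 0.0015 / 0.0057 = 0.26 standard errors.
- A shift of 0.26 standard errors would raise a nominal 5% two-sided error to about 5.8%. The 0.0008 mm case raises nothing under the null, because there g is the treatment effect itself and would be zero.

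A wider grid, k from 2 to 10% and g from 0.25 to 1.0 SD (0.015 to 0.06 mm), gives shifts from 0.02 × 0.015 = 0.0003 mm to 0.10 × 0.06 = 0.006 mm, or 2 to 38% of the planned difference. The top corner needs one patient in ten never to start and to differ by almost four times the planned effect.

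**The case against.** Several counter-arguments have force.

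- **A reader might infer that the last example empties the analysis set of everyone with follow-up data.** The documents do not support this. The examples illustrate protocol violations, the protocol requires the 24-month scan, and the same section plans an analysis of covariance on it. This is a drafting slip.
- **A reader might infer that diet-and-exercise controls, or all controls, would be dropped.** Study overview and design uses the word treatment for both arms, which makes that outcome unlikely to be intended. The article also gives no share of patients on diet and exercise alone.
- **Blinding.** The limitations paragraph of the Discussion says data are managed and analysed blinded, and Study organization and oversight says these tasks are carried out independently. This lessens the worry about discretionary exclusions. It does not cure the dose condition, which acts differently by arm whoever applies it; checking whether ipragliflozin was ever taken also reveals the arm.
- **The open-ended violation list.** The consent and registration examples do not depend on arm. A closed list and a per-protocol definition are details an article may leave to the SAP, so their absence is not part of this point.
- **The safety population.** The Safety section opens with "Based on the intention-to-treat the entire population". One might infer that an all-randomised efficacy set already exists and was passed over. That unclear sentence concerns recording adverse events and does not define such a set.
- **Size.** The illustration stacks assumptions: 5% never starting equals the whole dropout allowance, and 0.03 mm exceeds the planned effect. In addition, the primary analysis omits missing observations, so never-starters without a 24-month scan drop out under either definition. This argument stands and limits the point to a correction of unknown, probably small effect.

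**Conclusion.** The point holds as a defect in a rule the article states. The one-dose condition has no common meaning across these two arms, and its practical effect is to permit removal of ipragliflozin never-starters without a counterpart among controls. The third example is misworded and appears to mean baseline data.

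The size of the bias cannot be established from the article. Under the assumed 5% one-sided exclusion and a gap of 0.016 to 0.03 mm, it is 0.0008 to 0.0015 mm, up to about 0.26 standard errors. Direction is equally open: removing patients who would have progressed more favours ipragliflozin, and removing those who would have progressed less does the opposite. If few patients never start, the effect is negligible.

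**What to change.** - Define the efficacy set as all randomised participants with valid consent, analysed as allocated, with no dose condition in either arm.
- Reword the third example as baseline data collected after treatment started, and tie it to an event both arms share, such as randomisation. Place it in the definition of a sensitivity set, so that the main definition keeps its single exclusion.
- Use any set that omits never-starters or other protocol violators only for sensitivity analysis.

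This changes wording only and can be done in the SAP, which the article says is still to be developed. The cost is slight dilution. If 5% never start and progress like controls, the expected difference falls to 0.95 × 0.016 = 0.0152 mm. With 228 per arm the standard error is 0.06 × √(2/228) = 0.00562 mm, so power is about Φ(0.0152/0.00562 − 1.96) = 77%. Excluding those patients (about 217 against 228) would give 80%. The change does not recover never-starters who have no 24-month scan.
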